## Abstract

Upper airway cough syndrome (UACS) is a common cause of chronic cough characterized by upper airway symptoms, including nasal discharge and throat discomfort. Empirical treatments for UASC-induced chronic cough, such as first-generation antihistamines, have been used; however, the long-term use of these medicines has adverse effects. Therefore, we evaluate the efficacy, safety, and economic feasibility of Wolbigachul-tang (WBGCT), an herbal medication for UASC-induced chronic cough. This is a randomized, double-blind, active-comparator-controlled, parallel, and exploratory clinical trial. Thirty patients with UASC-induced chronic cough will be recruited and randomly allocated to the WBGCT and control groups in a 1:1 allocation ratio. The investigational medicine will be administered three times per day for 2 weeks (3 g of WBGCT at a time). The primary outcome measure is the cough symptom score measured at screening, before starting the trial, and after 2 and 4 weeks. Secondary outcome measures include the cough visual analog scale, nasal discharge score, questionnaire of clinical symptoms of cough and sputum, Leicester cough questionnaire-Korean version, integrative medicine outcome scale, integrative medicine patient satisfaction scale, and 5-level EuroQol 5-dimensional questionnaire, which will be assessed before starting the trial and after 2 and 4 weeks. This study aims to investigate the efficacy, safety, and economic feasibility of WBGCT in the treatment of chronic cough. Therefore, the results of this trial provide evidence for the application of WBGCT in the treatment of UACS-induced chronic cough.

## 1. Introduction

Cough is one of the most common symptoms of respiratory diseases and is classified as acute, subacute, or chronic, depending on its duration [1]. Among these, the importance of chronic cough lasting longer than 8 weeks has emerged because it has been correlated with decreased quality of life, including physical, mental, and social aspects, as well as complications such as vomiting, nausea, chest pain, urinary incontinence, anxiety, and depression [2,3]. Common causes of chronic cough include upper airway cough syndrome (UACS), cough-variant asthma, and gastroesophageal reflux disease, and of these, UACS is the most common cause of chronic cough [4], accounting for 19–25% of the causes of chronic cough [5,6].

UACS is characterized by a chronic cough with upper airway symptoms, including a sensation of nasal secretions in the throat, nasal stuffiness, rhinorrhea, and throat itching, resulting in physical and psychosocial complications [7,8]. The treatment of patients with UACS-induced cough depends on empirical therapy. When the cause of UACS, such as rhinitis or sinusitis, is obvious, treatment focusing on the cause should be administered. While specific causes may not be identified, medications that are effective in treating UACS-induced cough should be considered [9]. First-generation antihistamines or decongestants are empirically administered to patients with UACS-induced cough. If patients have persistent nasal symptoms, nasal steroids or anticholinergic agents should be administered [10]. However, evidence that antihistamines are effective in the treatment of UACS is insufficient, and long-term use of these medications has adverse effects, including drowsiness, fatigue, memory loss, and decreased concentration [11,12].

Previous studies have demonstrated the therapeutic effects of herbal medications in patients with UACS [13,14]. Wolbigachul-tang (WBGCT) is an herbal formula used to treat respiratory diseases such as asthma and allergic rhinitis [15,16]. It has been reported that WBGCT has antioxidant, anti-inflammatory, and antitussive effects on laryngeally-induced cough [17,18]. The hypothesized mechanism by which WBGCT has therapeutic effects against UACS-induced chronic cough is through the alleviation of upper airway inflammation. However, since the adverse effects of WBGCT including palpitation and insomnia have been reported [19], we will assess the safety of WBGCT, as well as its efficacy. In addition, to explore the possibility of using WBGCT with health insurance coverage, we will evaluate the economic feasibility of WBGCT by comparing it with Socheongryong-tang (SCRT), a health insurance-covered herbal formula used for respiratory symptoms. SCRT has been used for respiratory diseases, such as allergic rhinitis, asthma, and bronchitis [20,21], and has anti-inflammatory and anti-allergic effects that are promoted by inhibiting cytokine release, infiltration of inflammatory cells, and airway remodeling in animal models [22,23]. The safety of SCRT has been demonstrated in previous clinical trials and in vivo studies [24,25]. Considering its efficacy and safety, SCRT was selected as the investigational medicine in this study.

This study aims to investigate the efficacy, safety, and economic evaluation of WBGCT for UACS-induced chronic cough, a feasibility study to demonstrate its possibilities, including the duration of intervention, recruitment of participants, outcome measures, and effect size before this trial.

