## 2. Methods

### 2.1. Study Design

This is a randomized, double-blind, active-comparator-controlled, parallel, exploratory clinical trial to evaluate the efficacy, safety, and economic feasibility of WBGCT for UACS-induced chronic cough. Thirty participants will be recruited for this trial and randomly assigned to the WBGCT and control groups in a 1:1 allocation ratio. This trial consists of screening, 2-week treatment, and 2-week observation periods. The medications will be administered three times a day for 2 weeks. The detailed study design is summarized in Figure 1 and Table 1.

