### 2.4. Outcome Measures

#### 2.4.1. Primary Outcome Measures: Cough Symptom Score (CSS)

The CSS is a rating scale for cough frequency during the day and at night. The score for each question ranges from 0 to 5 (with the total score ranging from 0 to 10) [27]. CSS has been used to assess the severity of cough and the efficacy of therapy in many studies on cough [28,29]. In this study, the Korean version of the CSS will be used, which has proven its validity and clinical utility, as well as acceptable repeatability and responsiveness to changes in patients with chronic cough [30]. Participants will evaluate their cough symptoms twice a day using a cough diary (assessment of daytime CCS from 08:00 to 20:00 at 8 PM and assessment of nighttime CSS from 20:00 to 08:00 at 8 AM). CSS will be assessed at visits 1, 2, 3, and 4.

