#### 2.4.2. Secondary Outcome Measures

(1)Cough Visual Analog Scale (VAS).

The VAS evaluates cough severity and frequency. The score ranges from 0 to 10 (0 means “no cough” and 10 means “cough as severe as it could possibly be”) [31]. The VAS will be assessed on visits 2, 3, and 4.

(2)Nasal Discharge Score (NDS)

The NDS assesses the severity of two symptoms: nasal discharge (anterior nasal discharge score) and mucous globus sensation in the back of the throat (posterior nasal discharge score), ranging from 0 to 3 (0 = none; 1 = mild; 2 = moderate; 3 = severe) [6]. Since the symptoms of UACS include nasal symptoms, such as nasal discharge and rhinorrhea, symptoms related to nasal discharge will be assessed using the NDS in this trial [6]. The NDS will be evaluated on visits 2, 3, and 4.

(3)Questionnaire of Clinical Symptoms of Cough and Sputum (QCSCS)

The QCSCS is developed from the Clinical Asthma Measurement Scale in Oriental Medicine-V (CAMSOM-V) in the Traditional Korean Medicine Clinical Practice Guidelines for Antitussives and Expectorants, remodeled for cough and sputum [32,33]. The items for the QCSCS are as follows: (1) cough (frequency, intensity, and sensitivity), (2) sputum (frequency, volume, difficulty in coughing, appearance, and color), (3) activities of daily living, and (4) nighttime sleeping. Each item is measured using a 4-point scale, with a maximum total score of 40 points. The QCSCS will be assessed on visits 2, 3, and 4.

(4)Leicester Cough Questionnaire-Korean version (LCQ-K)

The LCQ-K evaluates the quality of life of patients with a cough and consists of 19 items divided into three parts: psychological, social, and physical aspects. Each item ranges from 1 to 7, with higher scores indicating a better quality of life. Previous studies have shown a correlation between the LCQ score and the severity of cough symptoms. The LCQ-K has been translated into Korean and verified for its validity and reliability [34,35]. The LCQ-K will be assessed on visits 2, 3, and 4.

(5)Integrative Medicine Outcome Scale (IMOS) & Integrative Medicine Patient Satisfaction Scale (IMPSS)

The IMOS evaluates symptom improvement. In this trial, the IMOS will be assessed by the investigators. The IMPSS is a rating scale used to assess treatment satisfaction of patients [36]. The scores on both scales range from 1 to 5. The IMOS and IMPSS will be evaluated on visits 3 and 4.

(6)5-level EuroQol 5-Dimensional Questionnaire (EQ-5D-5L)

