### 2.5. Safety Assessment

For the safety assessment, adverse events (AEs), vital signs, electrocardiograms, and clinical laboratory tests (complete blood count, liver function test, and urine analysis) will be assessed. AEs are harmful and unintended signs, symptoms, and diseases in patients taking investigational drugs, which do not necessarily imply a causal relationship with the investigational drugs. Vital signs and AEs will be assessed at every visit after the investigational medications are administered (visits 2, 3, and 4). The investigators will record the date of onset, severity, results of AEs, action taken against investigational medications, causal relationship between AEs and investigational medications, other suspected medicines, and treatments for AEs. When AEs occur, the principal investigator should conduct continuous follow-up until they disappear, or the patients are in a stable condition. All serious AEs will be reported to the principal investigator within 24 h.

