**Figure 2 healthcare-11-02733-f002:**
[figure not shown]
The potential mechanisms of ingredients in WBGCT for UACS-induced chronic cough. Previous studies demonstrated that the ingredients had anti-inflammatory, antioxidative, anti-allergic, antibacterial, and antiviral effects, affecting airway smooth muscle and lung tissue [43,44,45,46,47,48,49,50,51]. UACS; upper airway cough syndrome, WBGCT; Wolbigachul-tang.

**Table 1 healthcare-11-02733-t001:** Schedule of enrollment, interventions and outcome measurements.

	Study Period			
	Enrollment	Allocation	Post- Allocation	Follow-Up
Visit	1	2	3	4
Timepoint	−2 Weeks	0	Week 2 ± 4 Days	Week 4 ± 4 Days
Enrollment				
Informed consent	X			
Eligibility screen	X			
Allocation		X		
Demographic characteristics	X			
Social and economic characteristics	X			
Medical history	X			
Chest X-ray, EKG	X			
Vital signs	X	X	X	X
Pulmonary Function Test	X			
Paranasal Sinuses X-ray	X			
Interventions				
WBGCT				
SCRT				
Assessments				
Clinical laboratory test ^1^	X		X	
Pregnancy Diagnosis Test	X			
CSS	X	X	X	X
Cough VAS		X	X	X
NDS		X	X	X
Cough and sputum severity standard		X	X	X
LCQ-K		X	X	X
IMOS & IMPSS			X	X
EQ-5D-5L		X	X	X
PICCQ	X			
Adverse reaction assessment		X	X	X
Compliance test		X	X	

^1^ CBC (erythrocyte count, leukocyte count, differential count, hemoglobin, hematocrit, platelet count, and erythrocyte sedimentation rate); LFT (AST, ALT, γ-GTP, ALP, BUN, creatinine, total bilirubin, and glucose); and U/A (urine chemical test paper, and urine microscopy). Abbreviations. ALP, alkaline phosphatase; ALT, alanine aminotransferase; AST, aspartate aminotransferase; BUN, blood urea nitrogen; CBC, complete blood count; CSS, cough symptom score; EQ-5D-5L, 5-level EuroQol 5-dimensional questionnaire; γ-GTP, gamma-glutamyl transpeptidase; IMOS, integrative medicine outcome scale; IMPSS, integrative medicine patient satisfaction scale; LCQ-K, Leicester cough questionnaire-Korean version; LFT, liver function test; NDS, nasal discharge score; PICCQ, pattern identification for chronic cough questionnaire; SCRT, Socheongryong-tang; U/A, urine analysis; VAS, visual analog scale; WBGCT, Wolbigachul-tang.

**Table 2 healthcare-11-02733-t002:** Composition of Wolbigachul-tang and Socheongryong-tang.

Latin Name	Amount (g)
Wolbigachul-tang	
Ephedrae Herba	3.75
Zizyphi Fructus	0.67
Gypsum Fibrosum	1.25
Atractylodis Rhizoma	2.50
Glycyrrhizae Radix et Rhizoma	1.25
Zingiberis Rhizoma Recens	0.83
Socheongryong-tang	
Ephedrae Herba	0.30

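### Palpitation and insomnia are the stated reason for assessing WBGCT safety, yet the first scheduled AE assessment after dosing starts falls on day 10-18 of a 14-day course; two lines in the existing diary would capture them sooner

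*Protocol article*

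**What the plan says.** The Introduction of the protocol article gives the reason for looking at safety: "since the adverse effects of WBGCT including palpitation and insomnia have been reported [19], we will assess the safety of WBGCT".

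Section 2.1 fixes the exposure ("The medications will be administered three times a day for 2 weeks") and the periods ("This trial consists of screening, 2-week treatment, and 2-week observation periods").

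Section 2.5 fixes when safety is assessed: "Vital signs and AEs will be assessed at every visit after the investigational medications are administered (visits 2, 3, and 4". It also fixes what is written down: "The investigators will record the date of onset, severity, results of AEs, action taken against investigational medications", together with causality, other suspected medicines and treatment of the event. Serious AEs go to the principal investigator within 24 hours. The same section names electrocardiograms among the safety assessments.

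Table 1 places visit 2 at timepoint 0 (allocation), visit 3 at week 2 and visit 4 at week 4. Visits 3 and 4 each have a window of four days either side. The row "Adverse reaction assessment" is marked at visits 2, 3 and 4, vital signs at all four visits, and EKG at visit 1 only.

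Section 2.4.1 describes an instrument already in the participants' hands: "Participants will evaluate their cough symptoms twice a day using a cough diary", at 8 AM and 8 PM. Only cough scoring is described for it.

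**The concern.** Palpitation and insomnia are symptoms that the participant feels. They may be mild, may come and go, and may settle before anyone asks. If the first scheduled enquiry after dosing comes when the course is nearly or fully over, the count, the onset date and the relation to dosing depend on memory.

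The objective measurement that bears most on palpitation is weak for a related reason. The vital signs at timepoint 0 serve as baseline, those at visit 4 belong to the observation period, and those at visit 3 may be taken on or off drug with nothing described to tell the two apart.

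At stake is how far the AE comparison can answer the safety question that the Introduction raises. With 15 participants per arm, the classification of one or two people changes the picture.

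**Working it through.** **Inputs.** Course length: 2 weeks = 14 days (section 2.1). Visit 2 = day 0, visit 3 = day 14 ± 4, visit 4 = day 28 ± 4 (Table 1). Diary: two entries per day (section 2.4.1). Evaluable target: 12 per group, 20% dropout (section 2.2.2).

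**The plan's own figure.** 12 / (1 − 0.20) = 15 per group, 30 in total, as section 2.2.2 states. One participant is therefore 1/15 = 6.7% of an arm.

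**Timing of the first assessment after dosing starts**

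- Earliest visit 3: 14 − 4 = day 10. Share of the course elapsed: 10/14 = 71%.
- Nominal visit 3: day 14. Share elapsed: 14/14 = 100%.
- Latest visit 3: 14 + 4 = day 18. The course ended 18 − 14 = 4 days earlier.
- Days in the window: 18 − 10 + 1 = 9. Days after day 14: 15, 16, 17 and 18, which is 4 of 9. This counts permitted days; it is not a probability that a visit falls late.
- Visit 4: 28 − 4 = day 24 to 28 + 4 = day 32, which is 10 to 18 days after day 14.

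The recall interval at the first scheduled enquiry is thus 10 to 18 days.

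**What the diary offers.** 2 × 10 = 20 entry points by day 10 and 2 × 14 = 28 by day 14. A line completed at each entry has a recall interval of about half a day; a line completed each morning, one day.

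**Section 2.5 against Table 1**

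| Item | Section 2.5 | Table 1 |
|---|---|---|
| Visit 2 | Counted among the visits after medication is given | Timepoint 0, allocation |
| Electrocardiogram | Listed as a safety assessment | Visit 1 only, before allocation |

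If Table 1 is followed, there is no ECG after baseline, and visit 3 is the only vital-sign reading that could be on drug. If section 2.5 is followed on visit 2, a reading after a first dose might exist, but Table 1 does not show one.

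**What cannot be computed.** The documents give no AE rate and no rate of recall, so the number of events that a diary line would add cannot be derived. Sample size and power do not change.

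**The case against.** The strongest reply is that nothing here is a wrong figure. How AEs are elicited, what else the diary contains and what participants are told to report between visits are details that an article commonly leaves to the full protocol. Late enquiry is also not failed capture, since onset dates are recorded and events are followed until they resolve or stabilise.

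Much of this stands, and it rules out three stronger readings that a reader might infer:

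- *The site cannot learn of events between visits.* Not supported. The 24-hour rule for serious AEs implies a route outside visits, and the article does not say what participants are told about other events.
- *Insomnia would be scored as cough burden and lost as an AE.* Not supported. The sleep item of the cough and sputum questionnaire ("3) activities of daily living, and (4) nighttime sleeping") is an efficacy item, but section 2.5 defines AEs broadly and without requiring causality. Sleeplessness qualifies as an AE whatever that item scores.
- *A stated fraction of events would be missed.* Not supported. Any such fraction would be an assumption with no source in the documents.

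Nor can one say that AEs are not assessed at all before visit 3: Table 1 marks an assessment at visit 2. At timepoint 0, however, that can give only a baseline answer.

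What the reply does not remove is the printed schedule. Section 2.5 and Table 1 state the AE times explicitly, and the first one after dosing starts is visit 3. The 24-hour rule does not reach mild, non-serious palpitation or sleeplessness. An onset date given at visit 3 is itself recalled. If the full protocol already has diary items or interim contacts for AEs, the sponsor need only confirm it.

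**Conclusion.** The point holds as a modest design improvement. On the printed schedule, the two risks that the protocol names have their first scheduled assessment after dosing starts on day 10 to 18 of a 14-day course, and the visit 3 vital signs may be off drug. A twice-daily diary that could shorten the recall interval to a day or less is already in use.

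This rests on three assumptions: that Table 1 is right to put visit 2 before the first dose, that the course ends at day 14 whatever the date of visit 3, and that no interim AE contact exists in the full protocol. The effect on event counts is unknown.

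Separately, and without any assumption, section 2.5 and Table 1 disagree on the status of visit 2 and do not match on electrocardiograms. Both mismatches bear on palpitation.

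**What to change.** 1. Add two yes/no lines to the existing diary in both arms: palpitation since the last entry (morning and evening), and difficulty sleeping not due to cough (morning). Place them after the cough scores so that the primary outcome is recorded first.
2. Route positive entries through the trial's own AE reporting process.
3. Tabulate these solicited events by arm and day, separately from other AEs.
4. At visit 3, record the date and time of the last dose beside the vital signs, so that on-drug and off-drug readings can be separated.
5. Reconcile section 2.5 with Table 1: whether visit 2 precedes or follows the first dose, and at which visits an ECG is taken. The sponsor must say which text is intended.

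**Cost.** Two diary lines, one case report form field and one table. No extra visit, procedure or participant is needed, and the primary analysis is unchanged. Prompting will raise background reports in both arms, which is why solicited events are kept apart. Ethics approval dates from September 2022, so the change may need an amendment.

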## 2. Methods

### 2.1. Study Design

This is a randomized, double-blind, active-comparator-controlled, parallel, exploratory clinical trial to evaluate the efficacy, safety, and economic feasibility of WBGCT for UACS-induced chronic cough. Thirty participants will be recruited for this trial and randomly assigned to the WBGCT and control groups in a 1:1 allocation ratio. This trial consists of screening, 2-week treatment, and 2-week observation periods. The medications will be administered three times a day for 2 weeks. The detailed study design is summarized in Figure 1 and Table 1.

### 2.2. Participants

#### 2.2.1. Inclusion/Exclusion Criteria

The inclusion criteria are as follows: (1) men and women aged 19–70 years; (2) patients with symptoms of rhinitis or postnasal drip (rhinorrhea, nasal discharge, cough, or nasal itching); or with gross findings of pebble-like appearance in pharyngeal mucosa; or dripping mucus in the throat or with radiological findings of sinusitis in paranasal sinuses (PNS) X-ray; (3) patients with a score above daytime cough symptom score ≥ 2 points and nighttime cough symptom score ≥ 1 point; and (4) patients who voluntarily agreed to participate in this clinical trial in written form.

The exclusion criteria are as follows: (1) patients with abnormal findings that could cause cough on the result of chest X-ray; (2) patients with abnormal findings in pulmonary function test (forced expiratory volume (FEV) <80% predicted or forced expiratory volume in 1 s (FEV1)/forced vital capacity (FVC) <70%); (3) patients diagnosed with acute respiratory disease, including upper airway tract within 1 month; (4) patients diagnosed with chronic respiratory disease (chronic obstructive pulmonary disease, bronchial asthma, bronchiectasis, interstitial lung disease, or other chronic respiratory diseases) within 2 years; (5) patients diagnosed with gastroesophageal reflux disease within 1 year; (6) patients who take steroids, anti-leukotrienes, anticholinergics, long-acting β2 agonists, antihistamines, antitussives, and expectorants within 2 weeks before participation in this clinical trial; (7) patients who take proton pump inhibitors, histamine receptor antagonists, mucosal protective drugs, gastrointestinal motility promoters, antacids, antidepressants, anxiolytics, and lower esophageal sphincter agonists for treatment of gastroesophageal reflux disease symptoms within 2 weeks before participation in the clinical trial; (8) patients who have been taking or have taken angiotensin-converting-enzyme inhibitors within 4 months; (9) patients with liver or renal impairment (alanine aminotransferase, aspartate aminotransferase, alkaline phosphatase, and creatinine ≥ 2 times the upper normal limit at screening); (10) patients with generic disorders, such as galactose intolerance, Lapp lactase deficiency, or glucose-galactose malabsorption; (11) patients with comorbidities that interrupt the treatment of cancers or clinical significant disorders of the kidney, liver, psychiatric system, cardiovascular system, respiratory system, endocrine system, and central nervous system, which interrupt assessments of efficacy and safety or completion of the clinical study; (12) patients with unregulated hypertension (systolic blood pressure 160 mmHg ≥ or diastolic blood pressure 100 mmHg ≥ in relaxation period for 10 min); (13) patients with unregulated diabetes mellitus (fasting blood sugar ≥ 180 mg/dL); (14) patients with history of hypersensitivity reaction to materials of drugs used in this clinical trial; (15) patients with a history of alcoholism or substance abuse; (16) current smokers or patients with history of smoking more than 30 pack-year; (17) pregnant or lactating women; (18) patients who do not use medically acceptable contraception (e.g., intrauterine device with proven pregnancy failure rate in spouse or partner, simultaneous use of barrier method for men or women with spermicide, or surgical procedures, such as vasectomy, tubectomy, tubal ligation, or hysterectomy for oneself or one’s partner) during the period from obtaining consent to completion of participation in this trial; (19) patients who participated in other clinical trials within 30 days before participation in this clinical trial; and (20) patients determined by investigators to be ineligible to participate in this trial.
